## Abstract

The research aims to evaluate the effectiveness of a computerized cognitive training program in improving executive functions and attention in elementary school children, compared to a traditional paper-and-pencil intervention. The study has been formulated as a randomized controlled trial with pre- and post-intervention measures. For the study, third-grade children with typical development aged between 7 and 9 years will be recruited. Participants will be randomly assigned to the two study arms (control and experimental). The experimental group will participate in a computerized intervention using the NeuronUp cognitive stimulation platform for 8 weeks, twice a week. Sessions will be conducted using computers in the computer lab of the participating educational institution. The active control group will engage in paper-and-pencil cognitive training for the same duration and intensity as the experimental group. Evaluators will be blinded to the assignment, and participants will be blinded to the target intervention. Hypothesis testing will be conducted through ANOVA-MR, and logistic regressions will be implemented to assess the effect of socioeconomic variables on children's performance. These results are expected to contribute to the discussion on the opportunities and benefits offered by cognitive training programs on the cognitive development of typically developing children.

Specifications table

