For attention, two neuropsychological tests were selected: the d2 Attention Test and the Trail Making Test. The d2 Attention Test, developed by Rolf Brickenkamp [47], measures sustained attention and processing speed. It consists of a worksheet with several rows of the letters 'd' and 'p,' each accompanied by one, two, three, or four small dashes above or below. The task requires the participant to cross out all the 'd' letters with two dashes above or below, ignoring all other letters and marks. The activity is timed, with a 20-second limit for each row, and includes a total of 20 rows.

The Trail Making Test (TMT) [48] evaluates visual processing speed, sustained attention, and divided attention. The test consists of two parts: Part A involves a sheet with randomly distributed numbers that the subject must connect in ascending order as quickly as possible. Part B is similar to Part A but includes both letters and numbers. The subject must connect them in ascending order while alternating between numbers and letters [49]. For this study, the children's version of the TMT, which has fewer stimuli, will be used.•**Covariate measures**

Sociodemographic data for each participant will be collected through a sociodemographic characterization questionnaire. This questionnaire includes variables such as parents' level of education, access to technological and informational resources, family socioeconomic status, and family composition, among others. These data will be treated as covariates to observe the correlation of these variables with the performance of the participating children, thereby achieving better control of confounding variables.

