## Statistical analysis plan

A hypothesis test will be conducted using Mixed-Model Analysis of Variance of Repeated Measures (RM-ANOVA), followed by Bonferroni corrections to examine differences between groups. In this analysis, pre-test and post-test evaluations will act as the within-subject factor (repeated measures), while the comparison between the experimental and control groups will serve as the between-subject factor. Partial eta squared will be used to quantify effect size, assuming variables meet the assumptions of homoscedasticity and normality for parametric tests; otherwise, non-parametric tests will be employed.

To analyze the relationship between participants' performance and various sociodemographic variables acting as potential confounders, multivariate linear regression analysis will be conducted for numerical variables, and logistic regression analysis will be applied for categorical variables.

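### Logistic regression is assigned to categorical variables although no categorical outcome is described, and the separate regressions cannot deliver the confounder control that the article claims

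*Protocol article*

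**What the plan says.** Three places in the protocol article bear on this.

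- **Statistical analysis plan.** The arm comparison is a mixed repeated-measures ANOVA, with pre-test and post-test as the within-subject factor and arm as the between-subject factor. No covariate is named. A separate paragraph opens "To analyze the relationship between participants' performance and various sociodemographic variables acting as potential confounders" and continues that "multivariate linear regression analysis will be conducted for numerical variables, and logistic regression analysis will be applied for categorical variables".
- **Abstract.** Here "logistic regressions will be implemented to assess the effect of socioeconomic variables on children's performance". Linear regression is not mentioned.
- **Outcome measures, covariate measures.** The questionnaire covers "parents' level of education, access to technological and informational resources, family socioeconomic status, and family composition, among others". The article then says: "These data will be treated as covariates to observe the correlation of these variables with the performance of the participating children", and gives the result as "thereby achieving better control of confounding variables".

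**The concern.** There are two linked problems.

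First, the choice between linear and logistic regression is tied to whether unspecified variables are numerical or categorical. The variables that plainly differ in type are the sociodemographic ones, and the type of a predictor does not decide the model. If performance is the response, as the Abstract says, a logistic model needs test scores cut at a threshold. None is given, so it would have to be chosen later.

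Second, the article credits these regressions with controlling confounding. Relating a covariate to performance in one model does nothing to the arm effect estimated in another. A reader of the eventual report could believe that the arm comparison had been adjusted for parental education or access to technology when it had not. Access to technology could plausibly matter in a comparison of computer with paper training.

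**Working it through.** **Inputs.** Regression rule and arm model: Statistical analysis plan. Direction of the logistic model: Abstract. Outcomes and covariates: Outcome measures. Effect size 0.75, alpha 0.05, power 0.8, 29 per group: Table 1 in Sample size calculation.

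**1. Does any reading make the regression rule sound?**

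| Reading of the categorical variables | Result |
|---|---|
| Sociodemographic predictors | Wrong criterion. A categorical predictor enters a linear model as indicator terms. |
| Performance outcomes | The rule would be standard but has nothing to apply to. The measures are the Tower of London, Digit Span, Corsi, Visual Span, Stroop, WCST, d2 and Trail Making tests. No categorical endpoint or cut-off is defined, and the same section analyses the scores by ANOVA with partial eta squared and a normality check. |
| Sociodemographic factors as the response | Reverses the direction stated in the Abstract, where performance is the response. |

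None of the three works. The Abstract (logistic only) and the Statistical analysis plan (linear and logistic) also disagree.

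**2. Do the side regressions adjust the arm effect?** The arm model contains time, arm and, as usual in a mixed ANOVA, their interaction. The sociodemographic variables appear only in a separate analysis. The arm estimate is therefore the same whether or not that analysis is run, and the control claimed under Outcome measures does not follow from the analysis described.

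**3. Which imbalance would matter?** The hypotheses concern greater improvement. With two time points, the arm-by-time test compares mean change between arms. Suppose a factor x differs between arms by D on average.

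- If x shifts the score by b at both pre-test and post-test, its contribution to the difference in change is bD − bD = 0.
- If x alters change by g, its contribution is gD.

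Only factors related to change leave a chance difference in the planned contrast. It also follows that adding a covariate to the repeated-measures model as a main effect only would not alter the arm-by-time test. It must act on change, or enter a model of the post-test score.

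**4. What could adjustment be worth?** First, the plan's own figure. Reading 0.75 as a standardised mean difference, the normal approximation gives 2 × (1.960 + 0.842)² / 0.75² = 27.9, so 28 per arm. The exact two-sided two-sample t-test gives 28.9, so 29 per arm and 58 in total, with power 0.801. Table 1 is reproduced.

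If covariates explain a share R² of the outcome variance, the residual SD falls by √(1 − R²) and the effective effect size becomes 0.75 / √(1 − R²). The article gives no R², so these values are assumed, and the small loss of degrees of freedom is ignored:

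| Assumed R² | Effective effect size | Power at 29 per arm |
|---|---|---|
| 0 | 0.750 | 0.80 |
| 0.1 | 0.791 | 0.84 |
| 0.2 | 0.839 | 0.88 |
| 0.3 | 0.896 | 0.92 |

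The table takes a two-arm comparison of one score as its base, because that is what reproduces the sample size. It shows scale and does not predict the gain for any particular test.

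**The case against.** The strongest reply has four parts.

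*The wording is only loose.* The sentence does not say which side of the model the variables are on, and read as response type it is the textbook rule. The article also names tests without listing the scored index of each. The ambiguity is real, and that every outcome is numeric is an inference. But nothing described is categorical, and the Abstract makes performance the response, so the correction is still needed.

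*A fuller plan may put the covariates in the arm model.* The article says they are treated as covariates and does not exclude them from the ANOVA, and an article condenses. That would excuse a missing covariate list. It does not excuse the stated route to control, which is to observe correlations, nor the logistic rule, which a fuller plan would have to contradict.

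*Randomisation makes adjustment optional.* This stands. A reader might infer that the arm comparison is biased by leaving these factors out. The documents do not support that: allocation is randomised, chance imbalance is already reflected in the standard error, and a factor with a stable effect on level cancels in the change contrast.

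*Logistic regression does not touch the main analysis.* This also stands. A reader might infer that dichotomising scores would reduce the trial's power. The article proposes no median split or other cut, and the arm comparison stays in the ANOVA. Any loss of information would fall on the secondary sociodemographic associations, and without a cut-off it cannot be sized.

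**Conclusion.** The point holds in two limited parts. The logistic rule is wrong as written in the Statistical analysis plan section and the Abstract, and it affects a secondary analysis. The confounder-control claim under Outcome measures is overstated, because the arm model described contains only time and arm.

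The randomised comparison remains valid. The cost is forgone precision and less protection against chance imbalance in factors that affect change. Its size depends on how much variance the covariates explain, which the article does not say; the power range of 0.84 to 0.92 rests on an assumed R² of 0.1 to 0.3. The conclusion also assumes that the scored indices are numeric, as the planned ANOVA implies. This should be corrected before analysis, but it does not threaten the trial's main inference.

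**What to change.** 1. In the Abstract and the Statistical analysis plan, replace logistic regression with linear models of each test score, entering categorical sociodemographic factors as indicator terms. Label these associations exploratory. Keep logistic regression only if a categorical outcome and its cut-off are defined in advance.
2. Then do one of the following:
   - prespecify an adjusted arm comparison, regressing post-test score on arm, pre-test score and a short fixed list of covariates already collected (for example parental education and access to technology), at least as a stated sensitivity analysis beside the planned ANOVA; or
   - withdraw the confounder-control claim from Outcome measures and describe the covariates as explored only.

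No new data are needed. The cost is wording and a few degrees of freedom. For illustration, with 58 children a model with intercept, arm, pre-test score and three covariate terms leaves 58 − 6 = 52 residual degrees of freedom, against 58 − 2 = 56 for a plain two-arm comparison.

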## Ethical considerations

The study is registered with the Vice-Rectorate of Research-Creation, Innovation, Extension, and Social Projection of University of Tolima under code 50,119. The randomized controlled trial complies with the ethical parameters defined by the Helsinki Declaration [1], as well as the norms for health research established by the Colombian Ministry of Health [2] in Resolution 8430. Parents and guardians of the participating children will provide informed consent. This randomized controlled trial has been approved by the bioethics committee of University of Tolima, documented in act 10 of December 13th, 2022.

## Protocol validation

This article presents the protocol of a randomized controlled trial aimed at evaluating the effects of computerized cognitive training on executive functions and attention in school-aged children, compared to traditional pencil-and-paper cognitive training. The study is relevant and pertinent to the academic community for several reasons: 1) It contributes to the discussion on integrating cognitive training into school activities to support children's cognitive development. 2) It will help consolidate evidence on the impact of computerized cognitive training and pencil-and-paper training in typically developing school-aged children. 3) It explores whether the use of technological interventions in cognitive training yields different impacts compared to non-digital interventions. 4) It assesses the feasibility of integrating cognitive training programs into primary school curricula. 5) The designed protocol aims to ensure the quality of the collected evidence through thorough bias control. Among the measures to be implemented for bias control are blinding of evaluators to assignment, blinding of researchers responsible for the intervention to subject evaluation, blinding of participants to the target intervention, and randomization of subjects to both study arms. Synthetic data imputations will be employed to handle missing data in the study, opting for intention-to-treat analysis.

## Limitations

One of the limitations of the study is its reliance on school settings, which may be subject to changes in the institutional school calendar and technological constraints such as availability of electronic devices and access to high quality internet. Additionally, the use of a commercial platform poses another limitation, as the accessibility of such technological resources for cognitive training in educational institutions may be limited. However, the study aims to provide evidence supporting the development of new digital learning resources that could potentially be made openly available to teachers and education professionals.

## Data Availability

Data will be made available on request. Data will be made available on request.
